# Transfer of manualized CBT for social phobia into clinical practice (SOPHO-PRAX): a study protocol for a cluster-randomized controlled trial

**DOI:** 10.1186/1745-6215-13-70

**Published:** 2012-05-30

**Keywords:** Social phobia, Cognitive behavioral therapy, Remission, Phase-IV research, Training, Dissemination, Treatment, Outcome

## Abstract

**Background:**

Cognitive-behavioral therapy (CBT) is generally known to be efficacious in the treatment of social phobia when applied in RCTs, namely when the treatment manual is based on the Clark-Wells approach. However, little is known about the efficacy of manualized treatments in routine clinical practice (Phase IV of psychotherapy research). The present study (SOPHO-PRAX) is a continuation of a large multicenter randomized clinical trial (SOPHO-NET) and analyzes the extent to which additional training practitioners in manualized procedures enhances treatment effect.

**Methods/design:**

Thirty-six private practitioners will be included in three treatment centers and randomly designated to either training in manualized CBT or no specific training. The treatment effects of the therapies conducted by both groups of therapists will be compared. A total of 162 patients (*n* = 116 completers; *n* = 58 per condition) will be enrolled. Liebowitz Social Anxiety Scale (LSAS) will serve as primary outcome measure. Remission from social phobia is defined as LSAS total ≤30 points. Data will be collected at treatment begin, after 8, 15, and 25 sessions (50 min each), at treatment completion, as well at 6 and 12 months post-treatment.

**Discussion:**

The present CBT trial combines elements of randomized controlled trials and naturalistic studies in an innovative way. It will directly inform about the incremental effects of procedures established in a controlled trial into clinical practice. Study results are relevant to healthcare decisions and policy. They may serve to improve quality of treatment, and shorten the time frame between the development and widespread dissemination of effective methods, thereby reducing health cost expenditure.

The results of this study will not only inform about the degree to which the new methods lead to an improvement of treatment course and outcome, but also about whether the effects of routine psychotherapeutic treatment are comparable to those of the controlled, strictly manualized treatments of the SOPHO-NET study.

## Background

Social phobia (SP), also known as social anxiety disorder (SAD), represents a chronic and debilitating mental disorder characterized by persistent fears of one or more social situations in which the person is exposed to unfamiliar persons and expects to be scrutinized by others. The person affected fears acting (or showing anxiety symptoms) in a way that will cause embarrassment and humiliation
[1]. DSM-IV-TR criteria indicate that, though such fears are recognized as unreasonable and excessive, exposure to such feared situations may invariably trigger anxiety, which may escalate to a situation-bound or predisposed panic attack. The fears in social phobia can cause clinically significant distress or impairment in social, occupational, or other important areas of functioning
[1]. Epidemiological studies have also shown co-morbid psychopathology (other anxiety disorder, mood disorders, substance abuse) to be common for this disorder (for example
[2]).

Prevalence rates have been found to vary across countries. A recent study by Ruscio *et al.*[3] found estimates of lifetime and 12-month prevalence at 12.1% and 7.1%, respectively. In Europe, a lifetime prevalence of 6.65%, and a 12-month prevalence estimate of 2.0% were found
[4,5]. The age of onset tends to be located between preadolescence and early adulthood, for example between 10 and 16.6 years
[6]. Onset at an age later than 25 years appears to occur less frequently
[3,7].

Epidemiological studies have shown SP to be typically chronic in its course (for example
[8]). Full remission from SP symptoms, though infrequent, tends to occur within 8 years when no treatment is provided
[9,10]. Probably due to the overlap in the symptoms of shyness and SP (that is, heightened autonomic arousal in social situations (for example increased heart rate, blushing, sweating,
[11], social skills deficits, such as low eye contact)), avoidance of social interactions, and cognitions reflecting fear of negative evaluation
[12-14], those affected by the latter may not be easily detected and thus remain untreated
[6].

Development and dissemination of efficacious treatments for SP is therefore in clear demand. CBT for social phobia is generally efficacious (for example
[15,16]). RCT trials favoring the Clark-Wells approach
[17] show the highest effect sizes
[18,19], even outperforming standard pharmacological treatment
[18] and suggesting specifically this approach to be distributed to routine clinical practice. However, to date a large disconnect between research and practice appears to hinder the development of psychology, both as a science and as a profession. Access to evidence-based psychological treatments has become a growing problem in the last 10 years. In spite of the support by healthcare authorities, the urgently needed evidence and consensus regarding the success of implementation of such treatments, in addition to the measurement of successful training outcomes, continues to be missing
[20]. Specifically for social phobia, the quality and effectiveness of CBT in routine practice remains unknown.

To the best of the authors’ knowledge, there is also no current research: (1) directly examining the effects of additional training in a manualized and highly effective procedure on outcome in routine CBT for social phobia; and (2) testing the effectiveness of CBT for social phobia (in the control group), usually delivered in the private practices in Germany.

Hence, as a continuation of the Social Phobia Psychotherapy Research Network (SOPHO-NET,
[21]), the present study (SOPHO-PRAX) is designed as a multicenter randomized clinical trial based on a standard protocol and a set of standardized measures for the assessment and treatment of SP. The present study protocol aims at testing the potential of the Clark and Wells CBT approach to the treatment of SP evaluated in the main trial of this research cooperation
[21] in order to improve the effects of routine psychotherapies. It therefore appears important to investigate in detail to what extent such treatment methods can be transferred from controlled trials to the less structured setting of routine clinical care, and whether the healthcare system benefits from such developments. The rationale of this study thus represents Phase IV of psychotherapy research.

## Methods/design

### Study centers

The present study is being conducted by three trial sites, namely the Universities of Dresden ([name]. [name]), Frankfurt ([name]. [name]), and Göttingen ([name]. [name]), each coordinating at least 12 private practices.

### Participants

Patient inclusion and exclusion criteria are listed in Table
1. The sample fulfilling these criteria are considered representative for social phobia patients qualifying for treatment in an outpatient setting. Assuming a drop-out rate of 25% over a period of 2 years, a total of 162 patients are planned to be enrolled in the study (that is 54 patients in each center; see sample size calculation). Patients will only be able to enrol once in the present trial. Participants will be able to directly contact the trial centre in response to advertisements via the internet, flyers, or newspaper articles. Alternatively, they will be referred to by healthcare practitioners (that is, medical doctors or private practitioners in psychotherapy). Once the diagnostician confirms the patient’s eligibility for the study, the patient will select and contact a therapist from a list of candidates for treatment. Only private practitioners officially listed in the German chambers of psychotherapists will be recruited. Informed consent from both the therapist and the patient will be collected. All therapists will have to be certified in CBT. Inclusion criteria for therapists are broad (that is, any age and gender, living in the area of the trial center) as a function of the naturalistic aspects of the present trial. However, practitioners having recent training (within the last 5 years) in the Clark and Wells treatment of SP
[17] will be excluded from the study. Measures of allegiance to the treatment condition and professional experience will be collected via self-report of the therapists as well as via expert ratings of video-documented sessions.

**Table 1 T1:** Inclusion and exclusion criteria

**Inclusion criteria**	Diagnosis of SP (SCID-I)
	Liebowitz Social Anxiety Scale >30 (>60 for generalized subtype)
	Age 18 to 70 years
	SP must be primary diagnosis (most severe disorder according to ADIS-IV)
	SP patients with co-morbid disorders will be included, provided that SP is the primary diagnosis, thus ensuring a clinically representative sample as well as analyses of subgroups (for example, type of SP, patients with co-morbid depressive disorder)
**Exclusion criteria**	Psychotic disorder
	Prominent risk of self-harm
	Acute substance-related disorders
	Personality disorders except for avoidant
	Obsessive-compulsive or dependent personality disorder (SCID-II) organic mental disorder
	Severe medical conditions
	Concurrent psychotherapeutic or psychopharmacological treatment, with the following exception: specific psychopharmacological treatments (that is, tranquilizer, hypnotics, neuroleptics, phytopharmaceuticals, and beta-blockers prescribed as anxiolytics) should be terminated prior to therapy onset
	Anti-depressive medication represents no exclusion criterion as long it is reliably and stably consumed

### Interventions

The experimental intervention comprises training in outpatient CBT for private practitioners, following the manual by 
[name], Clark, and Ehlers [22]. The manual follows the model of Clark and Wells
[17] and prescribes interventions which are as follows: derivation an idiosyncratic version of the Clark and Wells model in cooperation with the patient; manipulation of self-focused attention and safety behaviors; application of video and audio feedback to modify distorted self-imagery; behavioral experiments in and out of the therapy room; attention shifts and interrogation of the social environment; identification and modification of anticipatory and post-event processing; identification of the patient’s dysfunctional assumptions and modification using cognitive restructuring. CBT treatment as usual will serve as the control condition. According to psychotherapy manuals (for example
[23]), up to 25 + 5 sessions are scheduled. See Figure
1 for trial flow. Practitioners will receive two separate blocks of training based on [name] *et al.*’s manual
[22], each block with a mean duration of 12 h. Practitioners in both groups will also be offered regular group supervision (with a mean duration of 2 h).

**Figure 1 F1:**
[figure not shown]
Intervention scheme/trial flow.

### Assessment

The time points of assessment are displayed in Figure
2.

**Figure 2 F2:**
[figure not shown]
**Time points of assessment.** 1) LSAS self rating, 2) LSAS observer rating.

Independent and trained SCID interviewers giving patient assessments are blind to the treatment condition. Assessments will be made at baseline, that is, prior to treatment onset (T1), at session 8 (T2), 15 (T3), and 25 (usually post-treatment, T4), at post-treatment (when treatment duration is longer than 25 sessions, T5). Every session is planned to have a 50-min duration. Follow-up assessments will take place 6 (T6) and 12 months (T7) after treatment; assessments at weeks 8 and 15 are performed to ensure intent-to-treat analyses. Primary endpoint: assessment after 25 sessions; secondary endpoint: post-treatment. Should treatment end at T4, measures for T5 will also be collected.

### Objectives and hypotheses

As a study combining the scientific benefits of randomized controlled trials (efficacy studies) and naturalistic studies (effectiveness research), its main objective is the analysis of the effects of additional training for private practitioners. Hence, the following question is investigated: does training in manualized treatment increase the effectiveness of psychotherapy for social phobia in natural settings?

We expect the effects of CBT on social phobia to be enhanced by training experienced therapists and by systematic transfer of innovative manualized treatments into practice. Thus, the specific hypotheses are as follows: (1) treatment effects achieved by private practitioners trained with the manualized procedures (Group 1) will be superior to those achieved by therapists who continue their standard treatment (Group 2); and (2) treatment duration (in terms of number of sessions between treatment onset and finalization) in Group 1 will be shorter.

### Outcomes

Endpoints and outcome measures were chosen in accordance with the main trial of the SOPHO-NET study
[21]. Outcome measures include internationally used valid and highly relevant measures of SP. The primary outcome measure will be the Liebowitz Social Anxiety Scale (LSAS
[24]). Remission from social phobia is defined as LSAS total scores ≤30 points. Secondary outcome measures include German versions of other standard scales for social anxiety (SPAI
[25], SPK
[26], SPV
[27], BSPS
[28]), depression (BDI
[29]), and a scale for quality of life and social functioning (EQ-5D
[30]). In addition we will assess emotional regulation (ASQ
[31]), helping alliance (HAQ
[32]), the subjective evaluation of sessions (STEPP
[33]), as well as the reaction to treatment (RTQ
[34,35]). During diagnostics, a rating on symptoms severity using the Clinical Global Impression scale (CGI
[36]) is also given. The majority of these measures will also be used in a related trial of manualized short-term psychodynamic therapy allowing for high comparability between both trials
[37]. Furthermore, patient sociodemographic data and costs of SP treatment are assessed using selected items of the German adaptation of the client sociodemographic and service receipt inventory (CSSRI; for example number of treatment sessions, days of work disability
[38]). All instruments will be applied in both groups of this trial. Using established cut-off scores for LSAS (≤30 points
[24]), the percentages of patients defined as remitted will be assessed and statistically compared between the group treated by specifically trained therapists and the group receiving standard CBT.

### Sample size calculation

The only study directly comparing performance of therapy delivered under RCT conditions and routine care refers to group CBT for social phobia
[18] and showed a small but significant advantage for the RCT therapies. The difference between the Clark trials
[17,18] and other controlled trials suggests a much higher difference in the to-be expected between-group effect sizes of our study but only under the improbable assumption that trained private practitioners will be comparably successful as the specialized therapists in the Clark trials. Sholomskas *et al.*[39], in a study directly testing the effects of additional training, but not in the field of SP, reported an average between group effect size of d = 0.69 when comparing therapists who were trained in a seminar plus supervision and therapists who used a manual without further training with regard to their performance in standardized role plays. However, this estimation does not directly refer to the expected effect sizes for the therapeutic benefit, which is the main outcome criterion of this trial. Given this inconsistent information, we choose to expect a more conservative effect size of d = 0.50 between Group 1 (trained therapists) and Group 2 (treatment-as-usual), for pragmatic reasons. We aimed at estimating the sample size needed for a dichotomous approach (remission rates according to the above defined criterion, LSAS <30). In order to assure comparability with the parallel trial for psychodynamic therapy
[37] we introduced the same conservative assumptions: (1) the ICC was set to 15% which is high compared to similar studies
[40]; and (2) for the primary analysis (ITT) drop-outs will be analyzed as patients with no remission. When assuming <50% remitters and an equal drop-out rate in both conditions, the absolute difference between remission rates will remain unchanged, but the relative difference will be much greater and will substantially enlarge the difference between treatments.

In contrast to Wiltink *et al.*’s study protocol
[37], the average number of patients in a cluster was assumed to be five, as we choose to collaborate more continuously with the included therapists. Please note that this is the only assumption differing from those made in
[37] resulting in a higher *a priori* sample size than in
[37].

In order to detect a difference between Groups 1 and 2 at α = 0.05 (one-tailed; see Discussion) with a power of 0.80, *n* = 58 patients per group are required according to the formula of Campbell *et al.*[40,41] for cluster-randomization, given that five patients per therapist will be treated (for a more comprehensive account, see
[42]):

$$N=2*{\left[\frac{\sigma (z_{\alpha }+z_{\beta })}{E}\right]}^{2}*\left[1+(m-1)\rho \right]=2*{\left[\frac{\left(z_{\alpha }+z_{\beta }\right)}{ES}\right]}^{2}*\left[1+(m-1)\rho \right]$$

(z_α_, z-value for probability of error type I alpha; z_β_, z-value for probability of error type II beta; σ, standard deviation of outcome; E, expected ES of outcome; m, mean observations for each cluster; ρ, Intracluster correlation coefficient (ICC); ES = E/σ, standardized effect size)

Given a conservative drop-out rate estimate of 25% (taking into account slightly elevated drop-outs in a practice study), a total of *n* = 162 patients are required to be allocated to the trial. Thus, *n* = 54 patients will have to be included in each center. According to data of the [name] *et al.*[43] study on social phobia, in which patients were recruited in a comparable setting of German psychotherapeutic care, 61% of 250 patients meeting the inclusion criteria can expected to be finally included. We estimate that not more than about 250 patients will have to be assessed for eligibility.

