### Statistical analysis

#### Primary analyses

The following hypothesis will be tested: H0: μ manualized ≤ μ standard *vs.* H1: μ manualized > μ standardwhere μ manualized and μ standard are the true remission probabilities in the manualized treatment group and the standard routine care group after the treatment period, respectively.

Remission rates will be compared between specifically trained and standard CBT group via logistic regression using covariates for treatment, sex of the therapist, and experience of the practitioner (as in
[37]). For repeated measures, as suggested by 
Wood *et al.*[46], random effects models will be fitted of outcomes taking into account potential drop-outs (for further reference, see
[42] and
[47]). Hypothesis 1 of this trial will be tested by the group*time interaction (with dummy variables coding the time effects at time points T4 to T7 as compared to baseline measurement).

Further analyses will include: comparison of remission rates across treatment groups at time points T4 to T7 using the chi-squared test of independence; cross-sectional analyses at T4 to T7 comparing both patients and therapists in the three study centers; analyses of covariance of outcomes at T4 to T7 considering patient variables, taking into account potential differences between patients recruited by trained *vs.* those recruited by non-trained therapists; and multiple regression analyses to test whether diverse covariates including process variables predict different treatment outcomes. Regression analysis will be applied to each treatment group separately. Should the results be similar, the sample will be pooled.

A descriptive analysis will be made on drop-outs and their covariates. Imputation methods will be considered if necessary following an assessment of the missing value structure
[46].

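### The 0.80 power is claimed for remission but calculated with a two-means formula and d = 0.50; no remission rates are given, so it is not shown for the remission test

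*Protocol article*

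**What the plan says.** All places are in the protocol article.

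- Sample size calculation gives the aim as "We aimed at estimating the sample size needed for a dichotomous approach (remission rates according to the above defined criterion, LSAS <30").
- The same section reviews standardised between-group effects from other studies, one of them on therapists' role-play performance outside social phobia (d = 0.69). It then concludes: "we choose to expect a more conservative effect size of d = 0.50".
- The formula is the cluster-adjusted one for two means, with ES = E/σ. The legend reads "σ, standard deviation of outcome; E, expected ES of outcome". Neither E nor σ is given a value.
- The claim is 58 per group, "In order to detect a difference between Groups 1 and 2 at α = 0.05 (one-tailed; see Discussion) with a power of 0.80", with five patients per therapist and an ICC of 0.15. Enrolment is 162 after allowing for 25% drop-out.
- The only remark on the level of remission is "When assuming <50% remitters and an equal drop-out rate in both conditions". In the primary intention-to-treat analysis, drop-outs count as not remitted.
- Under Primary analyses, the two parameters in the hypotheses "are the true remission probabilities in the manualized treatment group and the standard routine care group after the treatment period". They are compared by logistic regression.

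**The concern.** Power for comparing two proportions depends on the proportions. A standardised mean difference fixes that power only after a conversion rule and a control rate have been chosen, and the article states neither. If d = 0.50 is a shift of half a standard deviation in LSAS, cutting the scale at 30 discards information, and the effect left on the binary scale is smaller than 0.50.

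What is at stake is how a null result would be read. If the remission test has roughly even odds of detecting the expected benefit, a non-significant result says little about whether training helps. A reader who relies on the stated 0.80 would take it as fairly strong evidence of no useful effect.

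**Working it through.** **Inputs from the article:** one-sided α = 0.05 (z = 1.645), power 0.80 (z = 0.842), d = 0.50, m = 5, ICC 0.15, 58 per group, 162 enrolled, 25% drop-out, drop-outs scored as non-remission. Design effect = 1 + 4 × 0.15 = 1.6. An equal split of 162 gives 81 per arm.

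**Assumptions of mine:** control remission among completers of 15–40%; where d is read as an LSAS shift, a normal LSAS with equal spread in both arms.

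**Step 1. The plan's own figure.** 2 × (2.4865/0.5)² = 49.46, and 49.46 × 1.6 = 79.1, so 80 per group. The stated 58 does not follow. It would need a design effect of 58/49.46 = 1.17. At 58 per group with design effect 1.6, the effective n is 36.25 and power for means is Φ(0.5 × √(36.25/2) − 1.645) = Φ(0.484) = 0.69. This is a separate error. I note it only so that its effect is not charged to the remission question.

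**Step 2. Three readings of d = 0.50 on the remission scale**, with control rate p0 and trained-group rate p1:

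- SD shift: p1 = Φ(Φ⁻¹(p0) + 0.5). The arcsine effect is then only 0.36–0.40.
- Logistic: odds ratio = exp(0.5 × π/√3) = 2.48.
- Arcsine effect of 0.50: p1 = sin²(arcsin√p0 + 0.25).

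**Step 3. The planned analysis.** Scoring 25% of each arm as failures multiplies both rates by 0.75. It therefore also multiplies the absolute difference by 0.75, whereas the section says that difference stays unchanged. Effective n = 81/1.6 = 50.6 per arm. With q0 = 0.75p0 and q1 = 0.75p1,

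power = Φ{(q1 − q0)/√([q0(1−q0) + q1(1−q1)]/50.6) − 1.645}.

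Worked case, SD shift, 30% v 49.0%: the rates become 22.5% and 36.8%, the difference is 0.143 and the standard error is √(0.407/50.6) = 0.0896. Power is Φ(1.59 − 1.645) = 0.48.

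| Reading of d = 0.50 | p1 for p0 = 15 / 30 / 40% | Power, 81 per arm, ITT |
|---|---|---|
| 0.5 SD shift in LSAS | 29.6 / 49.0 / 59.7% | 0.44 / 0.48 / 0.47 |
| Logistic, odds ratio 2.48 | 30.4 / 51.5 / 62.3% | 0.47 / 0.56 / 0.54 |
| Arcsine effect 0.50 | 36.4 / 54.4 / 64.7% | 0.67 / 0.65 / 0.62 |

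**Step 4. Separating the two errors (SD-shift reading, 58 per arm, no dilution).**

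- Design effect 1.6: 0.69 for means, 0.45–0.53 for remission.
- Design effect 1.17, which would make 58 right: 0.80 for means, 0.55–0.64 for remission.

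The shortfall for remission therefore remains if the arithmetic behind 58 is put right.

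**Step 5. What the two-means calculation does support.** For continuous LSAS at d = 0.50 and design effect 1.6, power is 0.81 if all 81 per arm are analysed. It is 0.70 if 25% are lost (60.75 per arm).

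**The case against.** **The effect size may have been meant on a binary scale.** The article calls ES only a standardised effect size. With an arcsine effect of 0.50, the same formula is a usable approximation for two proportions, and this is the reading kindest to the plan. It stands as a possibility, and it is why the size must be given as conditional. It does not rescue the claim: power is 0.62–0.67 in the planned analysis and about 0.69–0.70 at 58 per arm with design effect 1.6. It passes 0.80 only if 81 per arm are analysed with no dilution, which is not the stated drop-out rule, or if 58 is taken with a design effect of about 1.17, which is not the stated ICC and cluster size.

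**Other sources may hold the rates.** The section adopts the assumptions of the parallel psychodynamic trial and refers elsewhere for a fuller account. That could explain where rates might be found. But the article prints the formula, the inputs and the power, and in that calculation no rate is used.

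**The cluster size is too large for the plan.** With 36 therapists, 162 patients is 4.5 each. The design effect would be 1.525 and the intention-to-treat power under an SD shift about 0.45–0.49. This is fair, but it changes little.

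**Two stronger readings are tempting.** A reader might infer that moving from means to remission alone takes power from 0.80 to about 0.5. It does not: at 58 per arm the first step, to 0.69, belongs to the design-effect arithmetic. A reader might also infer that the calculation concerns an endpoint which the primary analysis does not use. The article does not support that. Outcomes names LSAS itself as the primary outcome measure, and Primary analyses includes repeated-measures random effects models with a group-by-time test of Hypothesis 1. What can be said is that the calculation does not describe the remission test that it names.

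**Conclusion.** The point holds as a mismatch between the stated purpose of the calculation and its method. The 0.80 power is not shown for remission. With the article's own cluster size, ICC and drop-out rule, none of the three plausible meanings of d = 0.50 reaches it: about 0.44–0.48 for an SD shift, 0.47–0.56 for a logistic conversion and 0.62–0.67 for an arcsine effect.

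These ranges rest on assumed control completer remission of 15–40%, equal arms, a normal approximation and, for the first range, a normal LSAS. The article gives no rate against which to check them, so no single figure should be presented as the trial's true power. The difference between the cut-offs (<30 in Sample size calculation, ≤30 in Outcomes) is clerical and does not affect the calculation.

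**What to change.** - State the assumed remission rate in each arm, for all enrolled patients with drop-outs counted as not remitted, using the ≤30 cut-off throughout.
- Recompute power with the two-proportion formula and the design effect at 81 per arm, and replace the 0.80 claim for remission with the result. Enrolment need not change.
- Say that the d = 0.50 two-means calculation applies to continuous LSAS, with power of about 0.81 only if all 81 per arm are analysed and about 0.70 if 25% are lost.
- Correct the 58 per group as a separate item, so that the two causes of lost power are not merged.

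The cost is one recalculation and a few sentences. The stated power for remission will be lower, and a null remission result will have to be interpreted in that light.

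### Counting drop-outs as non-remitters shrinks the absolute remission difference by the drop-out fraction; the Sample size calculation says it stays unchanged, so the power of the ITT remission comparison is overstated

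*Protocol article*

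**What the plan says.** All of this is in the protocol article, mainly under Sample size calculation.

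- Effect: "we choose to expect a more conservative effect size of d = 0.50" between the trained and the usual-treatment groups. It is applied to binary remission: "We aimed at estimating the sample size needed for a dichotomous approach".
- Error rates: "at α = 0.05 (one-tailed; see Discussion) with a power of 0.80".
- Clustering: "the ICC was set to 15% which is high compared to similar studies", and "the average number of patients in a cluster was assumed to be five".
- Drop-outs: "for the primary analysis (ITT) drop-outs will be analyzed as patients with no remission". On the condition that fewer than half remit and drop-out is equal, the text adds that "the absolute difference between remission rates will remain unchanged, but the relative difference will be much greater", and concludes that the rule substantially enlarges the treatment difference.
- Numbers: 58 per group from the cluster formula, then "Given a conservative drop-out rate estimate of 25" per cent, giving 162 patients in all. The abstract identifies the 58 per condition (116 in total) as completers.

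**The concern.** The statement concerns the direction in which the main ITT rule moves the treatment effect. Setting an equal fraction of each arm to failure scales both rates down by the same factor. It does not subtract the same number of points from each. The rule therefore dilutes the absolute difference, while the protocol tells the reader that it strengthens the contrast.

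The sizing has the same gap. An undiluted d = 0.50 gives a number of completers, and the 25% is added as if drop-outs left the analysis. Under the ITT rule they stay in the denominator as failures. The remission comparison would then be run on a smaller effect than the one it was sized for. This matters for interpretation, because the Discussion itself warns that a negative result would not show equivalence.

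**Working it through.** **Inputs from the protocol.** One-sided α = 0.05 (z = 1.645); power 0.80 (z = 0.842); d = 0.50; ICC 0.15; m = 5; drop-out q = 0.25; 58 completers per group; 162 enrolled, so 81 per arm with equal allocation. Design effect (DE) = 1 + (5 − 1) × 0.15 = 1.60.

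**Assumption.** The protocol gives no remission rates. I vary control completer remission p0 and choose trained remission p1 so that 2·asin(√p1) − 2·asin(√p0) = 0.50. I read the protocol's condition of fewer than 50% remitters as applying to both arms. Then p1 reaches 50% at p0 = 26%, so the condition covers p0 up to about 26%.

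**Step 1: the plan's own figure.** 2 × [(1.645 + 0.842)/0.50]² = 49.5 per group, and 49.5 × 1.60 = 79.1, so 80 and not 58. A result of 58 needs DE = 58/49.5 = 1.17. Also 116/0.75 = 154.7, so 155 and not 162. These are separate errors. They matter here because they leave two candidate design effects, 1.60 and 1.17.

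**Step 2: the algebra.** With equal drop-out q, and drop-outs set to failure:

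- ITT rates: (1 − q)·p1 and (1 − q)·p0
- Absolute difference: (1 − q)·(p1 − p0)
- Ratio: p1/p0, unchanged

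**Step 3: example with p0 = 25%, p1 = 48.8%.**

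| | Completers | ITT, q = 0.25 |
|---|---|---|
| Trained | 48.8% | 36.6% |
| Control | 25.0% | 18.8% |
| Absolute difference | 23.8 points | 17.9 points |
| Ratio | 1.95 | 1.95 |
| Odds ratio | 2.86 | 2.50 |
| Arcsine effect | 0.50 | 0.40 |

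Reading the relative difference as an odds ratio does not help, because the odds ratio falls.

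**Step 4: power.** Power = Φ{(a − b)/√([a(1 − a) + b(1 − b)] × DE/81) − 1.645}, where a and b are the trained and control rates. For the diluted example at DE 1.60: 0.1787/0.0871 = 2.050, and Φ(2.050 − 1.645) = 0.66. Undiluted: 0.2382/0.0929 = 2.563, giving 0.82.

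| Control completer remission | Undiluted, DE 1.60 | ITT, DE 1.60 | ITT, DE 1.17 |
|---|---|---|---|
| 15% | 0.815 | 0.672 | 0.79 |
| 25% | 0.821 | 0.657 | 0.77 |
| 26% | 0.821 | 0.655 | 0.77 |
| 40% (trained 64.7%, outside the condition) | 0.822 | 0.618 | 0.73 |

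The ICC and m are unchanged between the undiluted and ITT columns at DE 1.60, and all 81 per arm are counted in both, so the fall comes from the dilution alone.

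**Step 5: sensitivity to cluster size.** 162 patients over 36 therapists is 4.5 each, so DE = 1 + 3.5 × 0.15 = 1.525. ITT power is then 0.67 to 0.69 for control rates of 15 to 26%.

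**The case against.** The strongest defence is an additive reading. Suppose the planned rates describe all enrolled patients and the coding moves the same number of percentage points to failure in each arm. Taking 10 points from each of 48.8% and 25% (an illustrative figure) leaves the difference at 23.8 points and raises the ratio from 1.95 to 2.59. The sentence would then be true, so it is too strong to say that it fails on every reading. But this reading needs drop-outs who would otherwise have remitted equally often in both arms. The protocol states neither that nor that d = 0.50 refers to everyone enrolled, and it sits badly with sizing on 116 completers and then inflating.

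Four stronger conclusions are tempting and are not supported:

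- **That power is this low even on favourable assumptions.** The protocol itself calls its ICC high. At DE 1.17 ITT power is 0.77 to 0.79, so 0.66 to 0.67 is not an upper bound.
- **That 0.62 belongs to the protocol's scenario.** It needs control remission of about 40% and trained remission of 64.7%, which breaks the protocol's own condition.
- **That the whole primary analysis is affected.** Under Primary analyses, Hypothesis 1 is also to be tested by a group-by-time interaction in random effects models that allow for drop-out. The failure-coding dilution does not carry over directly to that test.
- **That the sentence set the sample size.** The formula has no term for it, and deleting it changes neither 58 nor 162. What can be said is that the effect size was not reduced for the ITT coding.

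**Conclusion.** The point stands in a limited form. For a completer effect with equal drop-out, the sentence is wrong on both scales: at 25% drop-out the absolute difference is multiplied by 0.75 and the ratio is unchanged. The protocol does not say outright that d = 0.50 is a completer effect, but its sizing implies it.

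On the protocol's ICC of 0.15 and m = 5, with all 81 per arm analysed, power of the binary ITT remission comparison is about 0.66 to 0.67 instead of about 0.82, for control completer remission of 15 to 26%. That control range is my assumption. At DE 1.17 the power is still just under the stated 0.80, so the existence of a shortfall does not depend on which of the two design effects is meant, though its size does. The mismatch between 58 and the printed formula is a separate matter and should not be counted as part of this loss.

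**What to change.** 1. Delete the sentence, or correct it to say that under this rule with equal drop-out the absolute difference is multiplied by one minus the drop-out fraction and the ratio is unchanged. Remove the conclusion that the rule enlarges the treatment difference.
2. State whether d = 0.50 refers to completers or to all enrolled patients, and give the completer remission rates assumed in each arm.
3. Restate the power of the ITT remission comparison from the diluted rates, with 81 patients per arm and the clustering design effect. Do not also treat the 25% as excluded patients in that calculation.
4. Say that the restated power applies to the binary remission comparison and not to the group-by-time test.

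The work is a change of wording and one recalculation. The cost is a stated power below 0.80 at either design effect examined here, which the sponsor would have to report or address.
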